**Figure 1 f1:**
[figure not shown]
Study design. Recruitment pathway. All patients who are not eligible the STARS-RC06 trial will progress through these steps. pMMR, proficient mismatch repair. MDT, multidisciplinary team.

Additionally, we will collect biological samples from all participants during treatment, The time points are shown in **Figure 2**. Fecal samples will be stored at -80°C for 16*S* rRNA sequencing. Tumor tissue samples will be used for the detection of PD-L1 expression level, MSI and TMB in the central laboratory. And blood samples will be used for MSI and TMB detection. Freshly collected specimens, resection, needle aspiration biopsy, punch or clamp biopsy will be all acceptable.

**Figure 2 f2:**
[figure not shown]
Sample collection procedure. Blood and fecal samples will be used for next generation sequencing (NGS), and tumor samples will be used for immunohistochemical staining and NGS.

### Criteria for discontinuing or modifying interventions

If patients cannot tolerate consolidation therapy or experiences progression in efficacy evaluation, the subsequent treatment plan will be decided after discussion by the MDT and included in the follow-up. The specific treatment process is outlined in **Figure 1**. For grades III and IV chemotherapy-related adverse events (AEs), reduce the dose by 20% to 25%, as appropriate. All of immunotherapy-related adverse events (irAEs) were managed according to the NCCN Guidelines for Rectal Cancer (2022) for the management of immunotherapy toxicity (4). Drugs such as antihypertension, antidiabetes, painkillers and other symptomatic treatment are allowed. If a patient has hepatic injury or myelosuppression, hepatoprotectant, granulocyte colony-stimulating factor, and thrombopoietin may be used. The use of other anti-cancer drugs and traditional Chinese medicine is prohibited.

### Study endpoints and assessment

The primary endpoint of this trial is the pCR rate, defined as the percentage of patients who achieved pCR after nCRT in the eligible population. Secondary endpoints include 2-year sustained of cCR rate; CR rate (the rate of patients with sustained cCR for 2 years and pCR); MPR, which is defined as residual viable tumor (RVT) ≤10%; neoadjuvant rectal (NAR) score, which were calculated based on pathological and clinical staging (NAR=[5pN - 3(cT - pT) + 12]^2^/9.61); 3-year non⁃regrowth disease free survival; 3-year disease-free survival; 3-year overall survival; 3-year localized recurrence-free survival; 3-year distant metastasis free survival; 3-year stoma-free survival, anal sphincter preservation rate; surgical R0 resection rate and safety (adverse events during neoadjuvant therapy and 30 days after surgery, as well as tolerance). In addition, the study also has exploratory endpoints to further investigate potential factors related to antitumor therapy, such as infiltrating lymphocytes in tumor tissue, the structure of gut microbiome, and RAS/BRAF status.

The per-protocol set (PP) is defined as subjects who strictly adhered to the study protocol without major violations, completed all treatment and follow-up, and had measurable data for the primary endpoint (pCR). The modified intention-to-treat set (mITT) excludes participants who received no intervention or provided absolutely no post-baseline data. Patients achieving cCR who opt for Watch & Wait management are included in the mITT set for efficacy analysis.

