**Methods:**

This prospective, single-center, single-arm phase II trial aims to assess the pCR rate of neoadjuvant long-course concurrent chemoradiotherapy sequential 6 cycles CapeOX regimen combined with sintilimab in ‘high-risk/very high-risk’ LARC patients with mid-to-low location and with pMMR phenotype. The primary endpoint for this study is the pCR rate. Secondary endpoints include 2-year sustained of clinical complete response (cCR) rate; CR rate (the rate of patients with sustained cCR for 2 years and pCR); major pathological remission; neoadjuvant rectal score; 3-year non-regrowth disease free survival; 3-year disease-free survival; 3-year overall survival; 3-year localized recurrence-free survival; 3-year distant metastasis free survival; 3-year stoma-free survival, anal sphincter preservation rate; surgical R0 resection rate and safety (adverse events during neoadjuvant therapy and 30 days after surgery, as well as tolerance).

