### Study design

This prospective, single-center, single-arm phase II trial aims to assess the pCR rate of neoadjuvant long-course concurrent chemoradiotherapy sequential 6 cycles CapeOX regimen combined with sintilimab in mid-to-low location LARC with ‘high-risk/very-high-risk’ and with pMMR phenotype. The treatment process is showed in **Figure 1**. Enrolled patients will initially undergo long-course concurrent chemoradiotherapy, targeting the primary tumor area and regional lymphatic drainage area: 50 Gy/25 fractions/5 weeks with intensity-modulated radiation therapy or volumetric modulated arc therapy, alongside simultaneous capecitabine 825 mg/m^2^, twice daily, throughout the radiotherapy period. Following the completion of neoadjuvant concurrent chemoradiotherapy (7–10 days later), the subjects will receive 6 cycles of CapeOX combined with sintilimab treatment: sintilimab 200 mg intravenously on the day 1, oxaliplatin 130 mg/m2 intravenously on the day 1, and capecitabine 1000 mg/m^2^ orally twice daily from day 1 to day 14. Efficacy evaluations will occur every three cycles using DRE, HRMRI and endoscopy. Patients with progressive disease (PD) will undergo multidisciplinary team (MDT) discussion for alternative treatment strategies, while those with tumor regression and good tolerance will continue therapy. Patients whose tumors have not completely regressed after 6 cycles of consolidation treatment will directly receive surgical treatment. For patients evaluated as cCR, ‘Watch and Wait’ or surgery can be chosen based on MDT discussion and patient preference. The evaluation criteria of cCR according to ESMO guideline (2017), including no palpable tumor on DRE, no residual tumor or white scar under endoscopy, negative scar biopsy, and no residual tumor or residual fibrosis or residual wall thickening because of edema on HRMRI, and no suspicious lymph nodes on T2-weighted images (10, 14).

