### Follow-up

The follow-up methods include outpatient visits and telephone follow-ups. The follow-up schedule consists of assessments every 3 months for the first 2 years, followed by visits once every 6 months in the 3rd year, and subsequently, visits once every 1 year for the 4th–5th years. Procedure refer to ESMO Rectal Cancer Guidelines (2017) (10). Follow-up evaluations include, but are not limited to DRE, carcinoembryonic antigen measurements, endoscopy and biopsy, abdominal enhanced computed tomography, HRMRI, and anal cavity ultrasound.

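### The safety endpoint's only post-treatment window is tied to surgery, so patients who are not operated have no counted window after their last study dose

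*Protocol article*

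**What the plan says.** The list of secondary endpoints (Study endpoints and assessment) ends with "safety (adverse events during neoadjuvant therapy and 30 days after surgery, as well as tolerance". The Methods paragraph of the Abstract has the same definition: "surgical R0 resection rate and safety (adverse events during neoadjuvant therapy and 30 days after surgery, as well as tolerance". Two periods are named: on neoadjuvant therapy, and 30 days from an operation.

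Surgery is not universal in this design. Under Study design: "For patients evaluated as cCR, ‘Watch and Wait’ or surgery can be chosen based on MDT discussion and patient preference". Under Criteria for discontinuing or modifying interventions, for those who cannot tolerate consolidation or who progress, "the subsequent treatment plan will be decided after discussion by the MDT and included in the follow-up". Study endpoints and assessment keeps non-operated responders in the analysis, but speaks only of efficacy: "Patients achieving cCR who opt for Watch & Wait management are included in the mITT set for efficacy analysis".

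Sintilimab belongs to the last neoadjuvant component: after chemoradiotherapy, "the subjects will receive 6 cycles of CapeOX combined with sintilimab treatment", with sintilimab on day 1 of the cycle. The Follow-up section schedules "assessments every 3 months for the first 2 years" and less often afterwards. It names tumour assessments only, in a list that it calls non-exhaustive.

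**The concern.** A safety endpoint should give every treated patient a defined observation period that starts and ends relative to exposure. Here the part of the window that follows treatment depends on a later event, surgery, which some patients forgo because they responded well and prefer to avoid it, and others because they stopped early. Whether an event after the last dose counts is then decided by response and patient choice.

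At stake is a named secondary endpoint. The trial is single-arm and its new component is a PD-1 inhibitor given up to the final cycle. An adverse event that begins after that cycle counts if it falls in the 30 days after an operation, and does not count in a patient under Watch and Wait. The patients left with the shorter window include those who keep their rectum, a main aim of the approach.

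**Working it through.** **Step 1. Counted window by patient path, taking the endpoint wording literally.**

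- Residual tumour after 6 cycles, operated: on therapy, then 30 days after surgery. The interval between end of therapy and surgery is not named.
- Complete clinical response, chooses surgery: the same.
- Complete clinical response, chooses Watch and Wait: on therapy only. Whether a later salvage operation would open the 30-day window is not stated.
- Stops early or progresses, not operated: on therapy only.

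No section of the article supplies a window counted from the last dose. The section on discontinuing or modifying interventions says how immune-related events are managed, not for how long they are collected.

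**Step 2. Direction of the effect.** Compare the stated endpoint with one that runs to a fixed time after the last dose and adds 30 days after any surgery. Every event in the stated endpoint is also in the second, and the second may hold more. So the number of patients with a counted event under the stated endpoint is at most the number under the second. The difference is zero if no qualifying event begins in the uncounted time, and positive otherwise. Its size needs the rate of events that begin after the last dose, which the document does not give.

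**Step 3. The base of 40 patients.** Sample size states P0 = 0.16, P1 = 0.36, two-sided α = 0.05, power 0.80 and 20% dropout. The one-sample normal approximation gives

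n = [(1.960 × √(0.16 × 0.84) + 0.842 × √(0.36 × 0.64)) / 0.20]² = 31.5, rounded up to 32; 32 / 0.80 = 40.

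The stated 40 is reproduced. The point does not depend on it beyond using 40 as the number treated.

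**Step 4. How many patients could be affected.** The only figures in the document come from the centre's earlier study, in the Background:

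- 28 evaluable − 19 operated = 9 not operated.
- Cross-check: 14 complete responses (clinical and pathological) − 5 pathological = 9 clinical. The two counts agree.
- Share: 9 / 28 = 32.1%; exact (Clopper-Pearson) 95% CI 15.9% to 52.4%.
- Applied to 40: 40 × 0.321 = 12.9, about 13. Limits: 40 × 0.159 = 6.4 and 40 × 0.524 = 20.9, so about 6 to 21.

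Carrying this share over is an assumption. The earlier study gave at least 3 consolidation cycles and this one plans 6. The Background reports that complete response was positively correlated with the number of cycles, so the share could be higher here. The figure counts patients without a named window, not uncounted events.

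**The case against.** The strongest objection is condensation. The wording is a parenthesis in a one-sentence endpoint list in a journal article, and the full protocol may set a proper reporting period. Had the article been silent, that would settle the matter. But it states a window, twice and identically, and the window does not fit a design with a non-operative path. If the full protocol has a longer one, the two texts need to be reconciled.

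One could also read the neoadjuvant period generously, as running until surgery or the decision against it. That would close the gap before surgery, but it still gives a Watch and Wait patient nothing after the decision.

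Thirty days after an operation is a reasonable period for surgical morbidity, and it is not at fault for serving that purpose. The fault is that it is the only window after treatment.

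Three stronger readings are tempting and the documents do not support them.

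- A reader might infer that recording stops with the last cycle, so that late toxicity is missed and non-operated patients have no safety observation at all. The article does not say so. Visits continue every 3 months for 2 years, non-operated patients are not excluded from them, and the list of evaluations is open. What follows is only that such events are not counted in the endpoint.
- A reader might infer that a safety comparison of Watch and Wait with operated patients is invalidated. No such comparison is planned.
- A reader might infer that the toxicity of sintilimab is materially understated. That needs a rate of late events, and none is given. The Background reports no immunotherapy-related toxicity of grade III or higher in the earlier study, without stating over what period.

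**Conclusion.** The point holds as a defect in the endpoint definition. As worded, patients who are not operated have no counted adverse-event window after their last study dose, and the interval before surgery is not clearly covered for the others. Any resulting error is towards understatement. Its size cannot be estimated from the document and may be small. About 13 of 40 patients (range 6 to 21) would be affected, on the assumption that the non-operated share of the earlier study applies. The primary endpoint and the sample size are untouched. The change should be made because it is cheap and because safety is a named endpoint.

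**What to change.** Define the safety window for every treated patient, operated or not, from the first dose to a fixed time after the last dose of study treatment. The sponsor sets the length; it could, for example, coincide with one of the 3-monthly visits already scheduled. Add 30 days after any surgery, including later salvage surgery, and report surgical complications separately from treatment-related events. If the full protocol already has such a window, bring the endpoint wording into line with it.

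The cost is a change of endpoint wording, adverse-event pages at an existing visit, and slightly more data entry. Enrolment is described as ongoing, so for patients already past the end of treatment the events would have to be taken from visit records. The reported adverse-event rate may be higher than under the present wording.

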### Study population

All included patients required pathological immunohistochemical confirmation of rectal adenocarcinoma with intact expressions of all 4 MMR proteins, had mid-to-low location tumors (distal margin ≤10 cm from anal verge) verified by HIMRI, and were risk-stratified according to ESMO rectal cancer guidelines (2017) as ‘high-risk’ (cT3c/d or very low localization levators threatening, MRF-negative cT3c/d mid-rectum, cN1-N2 with extranodal involvement, EMVI-positive, or limited cT4aN0) or ‘very high-risk’ (cT3 with MRF involved, any cT4a/b, or lateral lymph node metastasis) (10). Participants willingly volunteered for this clinical study and provided written informed consent. Detailed inclusion and exclusion criteria are available in **Table 1**. The study commenced in October 2023 and is expected to end before December 2028. If all enrolled patients complete all treatment plans during this period, the study will be terminated. Study enrollment is ongoing, with the first patient recruited on October 31, 2023.

**Table 1 T1:** Patient inclusion and exclusion criteria.

Inclusion criteria:	Exclusion criteria:

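### The per-protocol set for pCR requires completed follow-up and a measurable pCR, so membership depends on events after surgery and excludes adherent Watch & Wait patients who are never resected

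*Protocol article*

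**What the plan says.** Under Study endpoints and assessment, the article defines PP by cumulative conditions: no major violations, and patients who "completed all treatment and follow-up, and had measurable data for the primary endpoint (pCR". The same section gives the primary endpoint as a rate, "defined as the percentage of patients who achieved pCR after nCRT in the eligible population". It does not tie that population by name to PP or mITT. For mITT it adds: "Patients achieving cCR who opt for Watch & Wait management are included in the mITT set for efficacy analysis". There is no matching sentence for PP.

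Three other sections bear on this:

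- **Follow-up** gives the only visit schedule, three-monthly for two years and six-monthly in year three, ending with "visits once every 1 year for the 4th–5th years".
- **Study population** gives first recruitment on 31 October 2023, says enrolment is ongoing, and says the study "is expected to end before December 2028".
- **Study design** makes non-operative management a permitted route: "For patients evaluated as cCR, ‘Watch and Wait’ or surgery can be chosen based on MDT discussion and patient preference".

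**The concern.** An analysis set for an endpoint read from the resection specimen should be settled by facts known at that time. Here membership stays open until follow-up ends. A patient operated on, with a pathology report on file, drops out of the PP pCR analysis if later lost or, on a natural reading, if the patient dies before the schedule is complete. If such losses are commoner among patients without pCR, the PP rate is too high. The PP result also cannot be fixed when the pCR data themselves are complete.

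The condition of a measurable pCR acts separately. A patient who receives all planned treatment, reaches cCR and takes the Watch & Wait option has broken no rule, yet fails the PP test for want of a specimen. The PP rate then describes operated patients only.

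**Working it through.** **The plan's own figure.** Sample size gives P0 = 0.16, P1 = 0.36, two-sided α = 0.05, β = 0.2 and 20% dropout. A one-sample z-test gives n = [(1.96·√(0.16·0.84) + 0.8416·√(0.36·0.64))/0.20]² = 31.5, so 32, and 32/0.80 = 40. The stated 40 is reproduced, and nothing here challenges it.

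**1. Effect of the follow-up condition.** Let p be the pCR rate among patients otherwise in the set, and r1 and r0 the proportions of pCR and non-pCR patients who complete follow-up. The PP rate is p·r1 / [p·r1 + (1 − p)·r0]. It equals p only when r1 = r0 and exceeds p when r1 > r0. The article gives neither quantity, so the direction is a matter of plausibility and the size is unknown.

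**2. Follow-up against the stated dates.** Take the end as 30 November 2028, the last day before December 2028. From 31 October 2023 that is five years and one month.

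Treatment time is 5 weeks (35 days), then 7–10 days, then six cycles. The article does not state the cycle length. For timing only, I assume 14 to 21 days.

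- Shortest: 35 + 7 + 6·14 = 126 days.
- Longest: 35 + 10 + 6·21 = 171 days.

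| Meaning of follow-up | Counted from enrolment | Counted from end of neoadjuvant treatment |
|---|---|---|
| Five-year schedule | entered by 30 November 2023 | none; the first patient reaches five years in March–April 2029 |
| Three-year endpoint horizon | entered by 30 November 2025 | entered by about 12 June to 27 July 2025 |

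With 21-day cycles, for example, the first patient ends treatment on 16–19 April 2024, and five years on is April 2029. The five-year reading leaves one month of entrants or nobody. The three-year reading leaves well over a year and a half of recruitment.

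**3. Effect of the measurable-pCR condition.** The Background reports the centre's earlier study: 28 evaluable patients, 19 with radical surgery, 5 with pCR, and 14 with cCR or pCR.

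- All evaluable patients: 5/28 = 17.9%.
- Operated patients only: 5/19 = 26.3%, a shift of 8.4 percentage points.
- Not operated: 28 − 19 = 9. Complete responders without pCR: 14 − 5 = 9.

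The two nines match. The article does not say that they are the same patients, but the figures suggest it. The shift therefore seems to come from removing clinical complete responders, not failures, and it says nothing about the follow-up condition. If the same share went unoperated here (an assumption), about 40·19/28 = 27 of 40 patients would have a specimen.

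**The case against.** The strongest reply is that PP is not shown to carry the primary result. The article uses the phrase efficacy analysis only for mITT, keeps Watch & Wait patients there, and assigns neither the hypothesis test nor any decision to PP. That stands. A reader might infer that the trial's main pCR result is biased, and the text does not establish this. Equally, neither set is named for the primary endpoint, so PP is not ruled out.

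Four further inferences go beyond the documents:

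- **That PP will be empty.** This needs the five-year reading. The longest endpoint horizon listed is three years, and the end date is only expected.
- **That 26.3% shows bias from dropping failures.** The nine patients removed appear to be responders.
- **That those lost to follow-up are mostly non-pCR.** No data on death or loss by pCR status are given. Patients who progress or cannot tolerate consolidation are kept under observation ("the subsequent treatment plan will be decided after discussion by the MDT and included in the follow-up"). They would fail the treatment-completion condition, but that is an ordinary PP criterion.
- **That every Watch & Wait patient is excluded.** One with regrowth and later resection would have a specimen, and the article does not say whether it would count.

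It can also be said that a condensed article leaves the use of PP for each endpoint to an analysis plan. That does not answer the point: the article states a positive rule and names pCR in it, and the rule as written is wrong for that endpoint.

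**Conclusion.** The point holds, at moderate severity. As written, PP membership for pCR depends on events after the endpoint is known, and patients with a known result can be dropped. The bias is plausibly upward but cannot be quantified from the article. The timeline conflict is conditional: one month of entrants or none on the five-year reading, and no near-emptiness on the three-year reading. The measurable-pCR condition is a distinct matter, illustrated by the move from 17.9% to 26.3% in the earlier study. It changes who is described and, on those figures, does not remove failures. If mITT is confirmed as the primary set, the harm is limited to PP results.

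**What to change.** - Delete the follow-up condition from the PP definition for pCR. Define PP by facts known up to surgery or the response decision: eligible, no major violation, protocol treatment completed, and response status determined by resection or cCR assessment.
- Name mITT as the primary set for pCR and PP as supportive.
- In mITT, keep every treated patient in the denominator. Count those without a pathological pCR as not pCR, whether through progression, toxicity, withdrawal or Watch & Wait. Watch & Wait patients are credited in the separate CR endpoint, which already combines cCR sustained for two years with pCR.
- Apply the same counting rule in PP. If a rate among operated patients is also wanted, label it as such.

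The cost is a change of wording, with no extra patients or data. The downside is that the reported pCR rate may be slightly less favourable, because each Watch & Wait choice counts as not pCR. That matches how the centre reported its earlier 5/28. Keeping every treated patient also retains anyone treated without post-baseline data, whom the present mITT wording removes, so that sentence needs aligning.

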## Background

Among all cancers, colorectal cancer ranks third in incidence and second in mortality worldwide (1). In China, the incidence of rectal cancer is on the rise, and most patients are diagnosed with locally advanced rectal cancer (LARC) at initial diagnosis (2), characterized by low rates of R0 resection and anal preservation (3). Preoperative neoadjuvant chemoradiotherapy (nCRT) has emerged as the standard treatment for mid-to-low location LARC (4). Statistical data indicates that nCRT achieves pathological complete response (pCR) rate of 8% - 24%, offering patients who achieved clinical complete response (cCR) potential ‘Watch and Wait’ opportunities (5–8). Preserving anal sphincter function while maintaining efficacy has become a key issue for LARC. Clinical trials demonstrate that total neoadjuvant therapy (TNT) can improve both pCR rates and organ preservation. However, in most trials, the pCR rate related to TNT was still lower than 30%, highlighting the need for novel strategies to enhance tumor response (9). The European Society for Medical Oncology (ESMO) guideline classify patients into different subgroups based on digital rectal examination (DRE), rectal high-resolution magnetic resonance imaging (HRMRI), and rectal intraluminal ultrasound (10). The guideline recommends adjusting treatment regimens for patients in different risk levels to achieve better efficacy and lower risk in precise treatment. While PD-1/PD-L1 inhibitors revolutionized care of colorectal cancer with deficient mismatch repair (dMMR) or microsatellite instability-high (MSI-H) phenotype, these represent only 8% - 10% of the cases. The remaining cases of proficient mismatch repair (pMMR) or microsatellite stabilization (MSS) phenotype could hardly benefit from immune checkpoint inhibitors (ICIs) treatment. Interestingly, it has been demonstrated that radiotherapy has the effect of stimulating the release of neoantigens and activating immunity (11). Building on this, the VOLTAGE study demonstrated that adding ICIs after nCRT could increase the pCR rate of MSS phenotype rectal cancer to 30% (12). At present, studies have shown that TNT combined with immunotherapy demonstrates better tumor regression and pCR rates, but its survival benefits such as DFS and OS need longer follow-up (13). Crucially, no solid evidence yet confirms whether adding immunotherapy significantly boosts pCR rates for mid-to-low location LARC patients with ‘high-risk/very high-risk’ according to ESMO guideline. Our center conducted a prospective, single-arm, observational study of long course concurrent chemoradiotherapy consolidation chemotherapy combined with PD-1 inhibitors, and the results are being submitted (STARS-RC03, NCT04906044). A total of 29 pMMR LARC patients received neoadjuvant long-course concurrent chemoradiotherapy followed by at least 3 cycles of CapeOX chemotherapy combined with PD-1 inhibitor. One patient discontinued treatment and was not effectively evaluated for efficacy. Our results showed that this regimen was safe and tolerated. Grade III toxicity was mainly associated with chemotherapy-induced hematological toxicity (51.71%, 15/29), and was reversed through active symptomatic treatment. No grade III or higher immunotherapy-related toxicity was observed. The pCR rate was 17.86% (5/28), and the overall complete response rate (cCR and pCR) was 50% (14/28). In 19 patients who undergone radical surgery, the major pathological remission (MPR) rate was 73.58% (14/19), and the R0 resection rate was 89.47% (17/19). Subgroup analysis found that the CR rate was positively correlated with the number of consolidation therapy, but the incidence of grades III or higher adverse events did not increase with the number of consolidation therapy. Building on these results, we propose the hypothesis that neoadjuvant long-course concurrent chemoradiotherapy sequential 6 cycles CapeOX regimen combined with PD-1 inhibitor further enhances the tumor pCR rate and has the potential to improve prognosis in mid-to-low location LARC patients with ‘high-risk/very high-risk’ and with pMMR phenotype.

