### Sample size

Based on evidence of the results of previous clinical trials summarized in the systematic review, the pCR rate of nCRT alone is approximately 16% (5), and the pCR rate of nCRT combined with ICIs is approximately 36% (13). Therefore, this study sets the null hypothesis (H0) at P0 = 0.16 and alternative hypothesis (H1) at P1 = 0.36. Using a two-sided test with α = 0.05 and β = 0.2, and accounting for a 20% dropout rate, the calculated total sample size is 40 patients. Computations were performed using PASS 2021 v21.0.3.

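### Watch & Wait patients have no specimen but stay in the mITT set of a pCR primary endpoint, and the stated 80% power makes no allowance for them

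*Protocol article*

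**What the plan says.** All references are to the protocol article.

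- **Study endpoints and assessment** defines the primary endpoint as "the percentage of patients who achieved pCR after nCRT in the eligible population". The eligible population is not defined further.
- **Study design** sends patients with residual tumour after six consolidation cycles to surgery. For patients with cCR, Watch and Wait "or surgery can be chosen based on MDT discussion and patient preference".
- **Study endpoints and assessment** gives two analysis sets. The per-protocol set requires, among other things, a measurable pCR result. For the modified intention-to-treat set it says: "Patients achieving cCR who opt for Watch & Wait management are included in the mITT set for efficacy analysis". Neither set is named as primary for pCR.
- The same section lists a composite as secondary: pCR together with cCR sustained for 2 years.
- **Sample size** tests P0 = 0.16 against P1 = 0.36, two-sided α = 0.05, β = 0.2, with 20% dropout, giving 40 patients. Watch & Wait is not mentioned there.
- **Background** reports the centre's pilot: 28 evaluable patients, 19 operated on, pCR 5/28, overall complete response 14/28. The pilot gave at least 3 consolidation cycles; this trial plans 6.

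**The concern.** A patient who avoids surgery cannot contribute a pCR. If that patient stays in the denominator, the measured pCR rate reflects how many complete clinical responders decline surgery as well as what the regimen does. If the patient is removed instead, the analysis loses a group selected for good clinical response. The document supports both readings and names no primary set.

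Two things are at stake. The stated power may not apply to the set in which Watch & Wait patients are kept. And in an open single-arm trial, a choice between mITT and operated patients made after the data are seen could move the conclusion.

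**Working it through.** **1. Reproduce the plan's figure.** Inputs from Sample size: P0 = 0.16, P1 = 0.36, two-sided α = 0.05, power 0.80, dropout 20%.

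n = [1.960·√(0.16·0.84) + 0.842·√(0.36·0.64)]² / 0.20² = 31.5, rounded up to 32; 32/0.8 = 40.

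The stated 40 is reproduced, so the arithmetic is not at fault.

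**2. Cut-offs.** The exact binomial test takes the smallest r with P(X ≥ r | 0.16) ≤ 0.025.

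- n = 32: r = 10 (size 0.024), power at 36% = 77%.
- n = 40: r = 12 (size 0.019), power at 36% = 83%.
- The z-test at n = 40 rejects above 40·[0.16 + 1.96·√(0.1344/40)] = 10.94, that is from 11 pCR. Its exact upper-tail size is 4.5% and its power at 36% is 90%.

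**3. What the pilot shows.** 28 − 19 = 9 patients were not operated on, and 14 − 5 = 9 complete responders had no pCR. The two counts agree, so 5/28 = 17.9% appears to keep nine unoperated complete responders in the denominator as non-pCR. Their share is 9/28 = 32%. The exact 95% interval for 5/28 is 6% to 37%. Among operated patients only, the rate is 5/19 = 26.3%.

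**4. Power in mITT with Watch & Wait counted as non-pCR.** Assume that 36% is the rate if everyone were operated on, and that a share w chooses Watch & Wait. The uptake range is an assumption; only 32% comes from the documents. If uptake is unrelated to pCR, the observable rate is 0.36·(1 − w).

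| w | observable rate | n = 32, ≥10 | n = 40, ≥12 (exact) | n = 40, ≥11 (z) |
|---|---|---|---|---|
| 0 | 36% | 77% | 83% | 90% |
| 10% | 32.4% | 62% | 68% | 80% |
| 20% | 28.8% | 45% | 49% | 63% |
| 32% (9/28) | 24.4% | 24% | 26% | 38% |

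At the other extreme, every Watch & Wait patient would have been pCR and the observable rate is 0.36 − w: 26%, 16% and 4%. Exact power at n = 40 is then 34%, 2% and about 0%.

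**5. Power if only operated patients are analysed.** At the pilot's share, 40·19/28 ≈ 27 patients remain. The exact cut-off is 9, and power at 36% is 68%.

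**The case against.** **The scoring is implied, not written.** The mITT sentence refers to efficacy analysis in general, which also covers the cCR, composite and survival endpoints, and nowhere does the protocol say that a Watch & Wait patient is a non-pCR. The analysis plan may settle this. That is fair. But a specimen-based endpoint leaves no other plain reading in mITT, and the pilot's 5/28 follows it. The power statement is in this document in any case.

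**P1 may already absorb the loss.** The 36% comes from a cited review that is not at hand, and its pooled rate may count unoperated patients. This cannot be checked, so the calculation is conditional on 36% being a rate with everyone operated on. What can be said is that no allowance is stated.

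**The 20% dropout may be meant to cover it.** Dropout inflation protects power only if the lost patients leave the denominator. Watch & Wait patients stay in mITT, and the pilot's share was 32%.

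**The z-test is more forgiving.** With the cut-off of 11 at n = 40, power is still about 80% at 10% uptake. That stands, but it needs all 40 patients evaluable, has an upper-tail size of 4.5%, and gives 63% and 38% at the higher shares.

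**Counting Watch & Wait as non-pCR is conservative** against a false positive, and sustained cCR and the composite are reported anyway. This stands as well, and it is why the fix keeps that scoring and asks for it to be stated.

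**Conclusion.** The point holds as a mismatch between the endpoint, the Watch & Wait option and the power statement. In mITT, the stated 80% does not hold once uptake is material: 68%, 49% and 26% at 10%, 20% and 32% uptake (exact test, n = 40), less if those opting out would have been pCR. This assumes that 36% is the rate with everyone operated on and that Watch & Wait scores as non-pCR. Because no primary set is named, the same pilot patients give 17.9% or 26.3%.

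Three stronger readings are tempting and are not supported.

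- A reader might infer that the trial is almost bound to fail, since exact power at a true rate of 5/28 is only 4% to 5%. That takes a small pilot as the truth. Its interval of 6% to 37% includes 36%, it required fewer cycles than planned here, and the Background reports that complete response rose with the number of consolidation treatments.
- A reader might infer that a better regimen must lower measured pCR. It may also raise pCR among operated patients; the net direction depends on uptake.
- A reader might infer that the composite must become primary. The documents give no null rate on that scale, and the pilot's 50% is not reported as sustained for 2 years. At n = 40 with P1 = 0.50, exact power is 78.5% for an assumed P0 of 0.28 and 44% for 0.35.

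**What to change.** 1. Name mITT as the primary analysis set for pCR, and replace or define the eligible population accordingly.
2. State that Watch & Wait patients count as non-pCR in that set.
3. Restate the power for 40 patients over a range of uptake, as in the table, and name the test and its cut-off.
4. State that the main conclusion will not rest on operated patients only; show that rate as supportive.
5. Report the composite already listed (pCR, or cCR sustained for 2 years) in the same mITT set as key secondary.

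The cost is a protocol amendment and a less favourable stated power. No new procedures are needed, because the components are already collected. Enrolment has been open since October 2023, so the change should be dated and made before outcomes are reviewed.

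Promoting the composite to primary is an option only if P0 and P1 are sourced on the complete-response scale and the change precedes any look at outcomes. It would also delay the primary result until the 2-year cCR assessment, and the sample size would have to be recalculated.
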